## Abstract

**Introduction:**

Lipid-lowering therapies, particularly statins, are central to the prevention of atherosclerotic cardiovascular disease. However, their effectiveness is often compromised by statin-associated muscle symptoms, leading to non-adherence, discontinuation and/or switching to alternative, more expensive therapies such as Proprotein Convertase Subtilisin/Kexin type 9 (PCSK9) inhibitors or bempedoic acid. Recent studies suggest that N=1-interventions may help distinguish true side effects from nocebo-driven symptoms and support reinitiation of statin therapy.

**Methods and analysis:**

The ‘N=1-studies In Statin-intolerance; Objectifying Nocebo Effects’ (NISONE) trial is a study with 249 patients with atherosclerotic cardiovascular disease or familial hypercholesterolaemia who stopped using two or more statins due to perceived symptoms. Participants are randomised (2:1) to an N=1-intervention or usual care. The intervention consists of four double-blind 6-week periods of statin (rosuvastatin 10 mg 1–2 tablets/day or atorvastatin 20 mg 1–2 tablets/day) or placebo treatment during which patients are required to record their symptoms through questionnaires in an application developed for this study. During the subsequent fifth treatment period, feedback on symptoms during the intervention periods is provided in a personalised report, which will be discussed by a healthcare professional. Statin continuation is encouraged if symptoms are similar for statin and placebo periods, but remains voluntary. Statin-intolerant patients in the usual care group will be treated according to the cardiovascular risk management guidelines. The primary outcome, the percentage of patients continuing their statin after 1 year, will be analysed using an odds ratio and its 95% Confidence Interval. Secondary outcomes will be analysed similarly, and cost-effectiveness will be assessed using seemingly unrelated regression equations, adjusted for baseline scores, costs and quality of life.

**Ethics and dissemination:**

The study protocol was approved by a Medical Ethical Research Committee in The Netherlands (EU CT-number 2023-507489-20-00). The study results will be disseminated via peer-reviewed medical journals, conference presentations, advisory boards and, if possible, by using various media channels.

**Trial registration number:**

This trial is registered in the EU Clinical Trials Information System (CTIS) (https://euclinicaltrials.eu/search-for-clinical-trials/?lang=en): 2023-507489-20-00.

KEY STRENGTHS AND LIMITATIONSThe N=1-studies In Statin-intolerance; Objectifying Nocebo Effects trial aims to investigate whether N=1-interventions can sustainably increase statin use in statin-intolerant patients and whether such interventions are feasible in clinical care.It will also assess patient-centred outcomes such as medication adherence, satisfaction, quality of life, trust in healthcare providers, as well as cost-effectiveness and acceptance among patients and healthcare providers.This trial will provide long-term (4 years) follow-up data, focusing on the effectiveness and feasibility of N=1-interventions to increase statin use in clinical practice.The study builds on previous N=1-intervention studies demonstrating the role of the nocebo effect in statin intolerance and their positive impact on statin use.Potential recruitment challenges are the possibility of reluctance of patients to participate and the focus of the study on high-risk patients, which may limit generalisability to those at lower cardiovascular risk.

## Introduction

 Lipid-lowering therapies (LLT), particularly statins, are essential in the management and prevention of atherosclerotic cardiovascular disease (ASCVD).^1^,^3^ Statins effectively reduce low-density lipoprotein cholesterol (LDL-C) levels and lower ASCVD risk by 20%–40%.^4 5^ Despite their proven efficacy and safety, 5%–17% of patients report statin-associated muscle symptoms (SAMS) under treatment with multiple different statins, a condition known as statin intolerance, often leading to non-adherence or discontinuation of therapy.^6^ This can compromise cardiovascular outcomes.^7^,^9^ Notably, the reported prevalence of statin intolerance varies depending on study design: double-blind placebo-controlled trials show similar rates for statins and placebo, while observational studies report a higher prevalence.^6 10^ This discrepancy is hypothesised to be partly attributable to the nocebo effect: negative expectations or prior experiences leading patients to misattribute their symptoms to statins.^11^ The National Lipid Association (NLA) defines statin intolerance as the inability to tolerate at least two different statins, with at least one causing any symptoms even at the lowest approved daily dosage.^12^

Recently published studies performed in statin-intolerant patients that included N=1-interventions showed that 85%–95% report no symptom difference between statin and placebo periods, and 50%–65% chose to restart statin therapy after reviewing their personal results.^13 14^ These findings suggest that N=1-interventions can not only clarify symptom attribution but may also support reinitiation of therapy. As such, this approach holds promise for reducing unnecessary discontinuation of statins and minimising reliance on costlier alternatives such as Proprotein Convertase Subtilisin/Kexin type 9 (PCSK9) inhibitors or bempedoic acid.^15 16^ We therefore designed the ‘N=1-studies In Statin-intolerance; Objectifying Nocebo Effects’ (NISONE) trial to evaluate whether implementing an N=1-intervention can promote statin use and assess its feasibility in clinical practice.

### Objectives

The NISONE trial will assess the long-term effects of N=1-interventions on statin use in statin-intolerant patients, extending follow-up to 4 years to evaluate sustained statin reinitiation. Outcomes include not only statin use but also patient-centred measures such as medication adherence, quality of life, satisfaction, medication perceptions, decisional conflict and trust in healthcare professionals. Additionally, the study evaluates the feasibility of implementing N=1-interventions through cost-effectiveness analysis and by assessing both patient and healthcare provider acceptability. If effective, the results will guide the integration of N=1-interventions into routine clinical care.

## Methods

The contents of this study protocol adhered to the Standard Protocol Items: Recommendations for Interventional Trials (SPIRIT) guidelines.^17^

### Study design

The study comprises a randomised controlled trial (RCT) that is conducted in different (university) hospitals in the Netherlands. The study has two treatment arms in the first half year of the study: an arm in which participants will undergo an N=1-intervention and an arm in which they will receive usual care. The randomisation between these two arms is open-label and participants are randomised among those arms in a 2:1 ratio respectively. A 2:1 randomisation ratio ensures that the majority of participants receive the N=1 intervention, allowing for better-powered analyses for outcomes in which patients identified through the intervention as intolerant due to statin therapy or intolerant due to misattribution and/or nocebo effects are compared with each other. The randomisation will be stratified on study site and the use of ezetimibe at baseline and is performed in the data management system of the study. An overview of this study can be found in figure 1. Inclusions for this study began in April 2025, and we anticipate that the final participant will complete their last visit by December 2032.

**Figure 1 F1:**
[figure not shown]
This figure provides an overview of the complete NISONE trial and the outcome measurements that are performed at the different moments during follow-up. m, months; NISONE, N=1-studies In Statin-intolerance; Objectifying Nocebo Effects; w, weeks.

Possible treatment sequences for the N=1-intervention are designed in a way to ensure a balanced exposure to statin and placebo treatment across the first four periods of the intervention (ie, two statin periods and two placebo periods). Also, a treatment sequence with two consecutive periods of placebo treatment is excluded to avoid a prolonged use of placebo treatment. Consequently, in the intervention-arm of the study, participants will undergo an N=1-intervention according to three different possible treatment sequences which are double-blinded (table 1). During the N=1-intervention, patients will receive two double-blinded periods of 6 weeks statin treatment (rosuvastatin 10 mg 1–2 tablets/day or atorvastatin 20 mg 1–2 tablets/day) and two periods of 6 weeks placebo treatment. Rosuvastatin and atorvastatin were chosen as the statins of choice due to their relatively high LDL-C lowering potency as compared with other statins. We specifically included the option of either a single daily dose of rosuvastatin 10 mg or atorvastatin 20 mg, or administering a double dose, to allow the treating healthcare professional (HCP) to individualise dosing and thereby optimise the likelihood of achieving guideline-recommended LDL-C targets. The type of statin and dose of the statin that is prescribed to the participant are at the discretion of the treating HCP. During the treatment periods, participants will record their (muscle) symptoms on a Visual Analogue Scale (VAS) at least three times a week. Furthermore, in the sixth week of every treatment period, participants will have their blood drawn for cholesterol levels. Cholesterol levels during these treatment periods are measured to provide participants with insight into their lipid levels under both statin and placebo therapy. This may help motivate patients to continue statin use and also allows verification that the correct treatment was taken during each period. This is important to address potential concerns from participants that treatment periods may have been inadvertently mixed up or that they may have incorrectly taken the assigned medication, which could otherwise lead to doubts about the validity of their individual results. After four periods of 6 weeks in total, participants will be switched to a fifth single-blinded treatment period with the active therapy (statin).

**Table 1 T1:** Treatment sequences in N=1-intervention arm of the study

Treatment sequence	Treatment period				Study results period
	1	2	3	4	
Sequence 1	S	P	S	P	S
Sequence 2	P	S	P	S	S
Sequence 3	P	S	S	P	S

S, statin; P, placebo.

During this fifth treatment period, participants will receive counselling on their individually reported symptoms and cholesterol levels during the treatment periods. They will receive a generated report consisting of several figures and graphs, which will among other things show the number of (muscle) symptoms during statin vs placebo periods, cholesterol levels across the different periods, the distribution of symptoms across different body regions and the extent to which symptoms affected their daily functioning, including any differences between statin and placebo periods. In addition, participants will receive a video that further explains their personal results. Subsequently, they will discuss their individual results in a consultation of approximately 30 min with their treating HCP. During this consultation, the results will be reviewed in detail and further interpretation will be provided, including whether the findings are suggestive of statin-attributable symptoms or symptom misattribution and nocebo effects. A 10 mm higher VAS during statin use is considered as the threshold to attribute the symptoms to statin use.^18 19^ After counselling, statin continuation is advocated if symptoms cannot be attributed to the statin, but it is voluntary and at the discretion of the participant. Participants will be treated according to the clinical guideline and prescribed a PCSK9i if necessary.

In the usual care arm of the study, participants will be treated according to the national cardiovascular risk management (CVRM) guidelines and reimbursement criteria for PCSK9 inhibitors.^20^ When patients with Familial Hypercholesterolaemia (FH) and/or ASCVD report side effects to at least three statins, they are considered statin intolerant as according to Dutch criteria and they qualify for reimbursement of PCSK9i.^21^ At the start of the intervention period, the HCP will discuss the prevalence of SAMS and the strong association with the nocebo effect as this is also stated in the international guidelines on cardiovascular disease prevention.^22^ The HCP will advocate statin use and attempt to rechallenge the patient with a statin or will prescribe another form of LLT, for example, a PCSK9i.

All HCPs who participate in this study will be trained to provide information on the nocebo effect to study participants. In this training, HCPs will receive practical tips focusing on communication about the nocebo effect. This training will be provided by the study coordinator (RM) and two dedicated behavioural psychologists involved in this project, one of which was also a patient advocate that was involved in the study.

### Study treatment

In the treatment arm of the N=1-intervention, participants will be administered tablets of rosuvastatin 10 mg 1–2 tablets/day or atorvastatin 20 mg 1–2 tablets/day along with their corresponding placebo tablets. These generic tablets have been developed and manufactured by Apotheek A15 (Gorinchem, The Netherlands) under a Good Manufacturing Practice license and the medication will be supplied to us. We will conduct two separate studies to demonstrate bioequivalence of atorvastatin and rosuvastatin with the marketed products (Lipitor and Crestor respectively) as comparator.

### Study population

Our study population will consist out of adult patients at high risk of ASCVD based on having FH or at very high risk based on having a diagnosis of previous ASCVD. All patients eligible for inclusion reported statin-related side effects while on ≥2 statins. The study will be conducted in at least 11 hospitals in The Netherlands, of which the academic medical centre of the Erasmus MC is the coordinating centre. Exclusion criteria for this study are:

a contra-indication for statin therapy;any condition that causes severe chronic muscle pain (ie, myopathy or myositis);a history of severe mental illness;a history of liver cirrhosis or severe renal insufficiency;an ASCVD event in the past 3 months;an inability or insufficiency to fill in the digital questionnaires;a clinical judgement of the HCP that LLT cannot be withheld in a patient with a recent ASCVD event in the past 12 months;the clinical judgement of the HCP that LLT is no longer relevant for the prognosis of the patient;the clinical judgement of the HCP that participation in the study is unethical or unwanted.

### Recruitment of patients

Patients will be recruited via the outpatient clinics of all participating centres in this study. Recruitment will take place through cardiology and vascular medicine clinics in regional hospitals and academic medical centres, as these specialists are the only healthcare professionals authorised to prescribe PCSK9i to adults in the Netherlands. Potential participants will be asked whether they are interested in participating in the trial after receiving information about the study from their treating healthcare professional. They will be given at least 1 week to consider whether or not they wish to participate. With the consent of potential participants, reasons for non-participation will be recorded in order to assess both the proportion of eligible patients who agree to participate and the reasons for declining participation.

### Measurements and data collection

An overview of the study assessments at different moments during follow-up can be found in figure 1. During the study, participants will receive follow-up by means of clinic visits and by means of digital surveys. During study visits, HCPs will measure blood pressure, heart rate, weight, waist circumference and physical activity. They will also record lifestyle habits and record all medication dispensing data of the pharmacy and (changes in) medical history. HCPs will record their acceptability of the intervention using a questionnaire at 6, 12 and 24 months after randomisation.

During the 4 years of follow-up, participants will be asked to complete a survey on multiple timepoints of the study (figure 1). All items that these questionnaires consist of are:

demographics;self-reported medication use;barriers to medication adherence (open-ended question);reasons for stopping medication (open-ended question);changes in lifestyle (open-ended question);participant acceptability of N=1-intervention (self-made, non-validated questionnaire with statements about acceptability on a 5-point Likert-scale; disagree-agree);5-item Medication Adherence Reporting Scale (MARS-5);EuroQoL-5 Dimensions-5 Levels (EQ-5D-5L);Set of Brief Screening Questions (SBSQ);Beliefs about Medicines Questionnaire (BMQ);Patient Experiences and Satisfaction with Medication (PESaM);Decisional Conflict Scale (DCS);Wake Forest Physician Trust Scale (WFPTS);Psychological Inventory of Financial Scarcity on 4 items (PIFS-4);iMTA Medical Consumption Questionnaire (iMCQ);iMTA Productivity Costs Questionnaire (iPCQ).

### Planned outcomes

The primary outcome of the study is the incidence of self-reported statin use at 12 months after randomisation, which is a binary outcome measure (yes/no). We specifically chose this outcome as the primary endpoint because the main objective of the study is to determine whether N=1-interventions, compared with usual care, can increase statin use in patients in routine clinical practice. We considered the 12-month timepoint to be the most appropriate to evaluate this outcome, as we believe this timepoint, approximately 6 months after completion of the N=1-intervention, best reflects patients’ willingness to continue statin therapy in the longer term, beyond the immediate influence of the intervention. Secondary outcomes of this study are focused on use of cholesterol-lowering medication at different timepoints, cholesterol levels at different timepoints, cost-effectiveness, satisfaction with medication and multiple outcomes that assess the applicability of N=1-interventions in clinical care. All secondary outcomes that are studied are:

statin use;PCSK9i use;LDL-C levels;quality of life (EQ-5D-5L questionnaire);reported symptoms;cost-effectiveness (iMCQ and iPCQ questionnaire, among others);views on medication (BMQ questionnaire);satisfaction with statins (PESaM questionnaire);decisional conflict (DCS questionnaire);trust in the HCP (WFPTS questionnaire);HCP satisfaction with intervention (self-made, non-validated questionnaire with statements about acceptability on a 5-point Likert-scale; disagree-agree);treatment concordance during intervention;physical and mental complaints during intervention.

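### The primary outcome is self-reported statin use in an open-label comparison with more intensive counselling in one arm, and the dispensing data already collected have no stated role in checking it

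*Protocol article*

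**What the plan says.** The Planned outcomes section of the protocol article defines the endpoint: "The primary outcome of the study is the incidence of self-reported statin use at 12 months after randomisation", as yes or no. The survey items under Measurements and data collection include self-reported medication use. The Data analysis plan compares the arms with an odds ratio and its 95% confidence interval.

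On blinding, the Study design section says: "The randomisation between these two arms is open-label". The double-blinding inside the N=1 arm conceals which period is statin and which is placebo. It does not conceal the arm.

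On encouragement, the text after Table 1 describes both arms. In the N=1 arm there is an individual report, an explanatory video and a consultation of about 30 minutes, and then: "After counselling, statin continuation is advocated if symptoms cannot be attributed to the statin, but it is voluntary". In usual care the professional discusses muscle symptoms and the nocebo effect, and: "The HCP will advocate statin use and attempt to rechallenge the patient with a statin", or prescribes another lipid-lowering drug.

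On objective data, Measurements and data collection says that at study visits the professionals will "record all medication dispensing data of the pharmacy". The article does not link these data to the primary outcome. Planned outcomes gives reasons for choosing statin use and for choosing 12 months, but none for taking it from self-report.

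**The concern.** The answer to the primary question comes from a participant who knows the allocation. In the N=1 arm that participant has logged symptoms through four treatment periods, seen a personal report and discussed it at length. Someone shown that the symptoms were not due to the statin, and then advised to continue, may be readier to answer yes than someone given general advice. If so, part of the difference between the arms would be a difference in reporting, and the trial would credit it to the intervention. The stated aim is to increase statin use. A supply record bears on that independently of what the participant says, and it is already being collected.

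**Working it through.** **Inputs.** From Sample size calculation: 12% usual care, 30% N=1, two-sided alpha 0.05, power 80%, 2:1 allocation, 25% drop-out, 247 needed (249 funded). The article gives no misreporting rates, so those below are assumptions shown over a range.

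**Step 1: reproduce the plan's figure.** Pooled-variance formula for two proportions, no continuity correction. Mean rate = (0.12 + 2×0.30)/3 = 0.24.

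n(usual care) = [1.960·√(0.24×0.76×1.5) + 0.842·√(0.12×0.88 + 0.30×0.70/2)]² / 0.18² = 61.49.

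Total = 3×61.49 = 184.46, rounded up to 185; 185/0.75 = 246.7, rounded up to 247. The stated figure reproduces. Rounding per arm gives 62 + 124 = 186 evaluable, with power 80.4%.

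**Step 2: observed rate under over-reporting.** If true use is p and a share f of non-users report use, the observed rate is p + (1−p)f. With p = 0.12, f = 5% gives 0.12 + 0.88×0.05 = 0.164, and f = 8% gives 0.190.

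**Step 3: chance of a significant result favouring N=1 when true use is 12% in both arms.** Probability = Φ[(d − 1.960·s0)/s1], where d is the observed difference, s0 the pooled standard error and s1 the unpooled one, at 124 vs 62.

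Worked case, 5% vs 0%: d = 0.164 − 0.120 = 0.044. Pooled rate = (124×0.164 + 62×0.12)/186 = 0.1493, so s0 = 0.0554 and s1 = 0.0530. Then (0.044 − 1.960×0.0554)/0.0530 = −1.22, and Φ(−1.22) = 0.111.

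| Over-reporting, N=1 vs usual care | Observed use | Odds ratio | Chance of false benefit |
|---|---|---|---|
| 0% vs 0% | 12.0% vs 12.0% | 1.00 | 2.5% |
| 2% vs 0% | 13.8% vs 12.0% | 1.17 | 4.9% |
| 5% vs 0% | 16.4% vs 12.0% | 1.44 | 11.1% |
| 8% vs 0% | 19.0% vs 12.0% | 1.72 | 21.3% |
| 5% vs 2% | 16.4% vs 13.8% | 1.23 | 6.3% |
| 5% vs 3% | 16.4% vs 14.6% | 1.14 | 4.7% |
| 8% vs 3% | 19.0% vs 14.6% | 1.37 | about 10% |
| 8% vs 4% | 19.0% vs 15.5% | 1.28 | 8.0% |
| 8% vs 5% | 19.0% vs 16.4% | 1.20 | 6.1% |
| 5% vs 5% | 16.4% vs 16.4% | 1.00 | 2.5% |

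**Step 4: equal over-reporting when the planned effect is real.** With f = 10% in both arms, N=1 shows 0.30 + 0.70×0.10 = 37.0% and usual care 0.12 + 0.88×0.10 = 20.8%. The odds ratio falls from 3.14 to 2.24, and power from 80% to 62%.

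**The case against.** Three stronger readings are tempting, and the article does not support them.

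*The pressure to say yes exists in one arm only.* It does not. Usual-care professionals also raise the nocebo effect, advocate a statin and attempt a rechallenge. All participating professionals receive the same communication training, and Sample size calculation expects some spill-over into usual care. Advocacy in the N=1 arm also depends on the individual result. What remains is a difference in intensity, so the rows with zero over-reporting in usual care mark the unfavourable end of the range.

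*Nothing planned could reveal the problem.* LDL-C, statin use and PCSK9 inhibitor use are secondary outcomes. Reported statin use without a matching LDL-C would be a warning sign. The signal is indirect, because other lipid-lowering drugs also lower LDL-C and the secondary statin-use outcome names no data source.

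*The bias is known to favour the intervention.* It is not. No misreporting rate is given, and equal over-reporting works the other way when there is a true effect.

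It is also fair to say that the 12-month assessment falls about six months after the N=1 periods end, which may soften any pressure to please, though allocation is still known. Dispensing has its own error: a patient who stops because of symptoms may hold tablets that are never taken. Finally, the full protocol and any analysis plan are not shown and may already contain a dispensing-based check, so its absence from the article is not the point. The point is that the article fixes self-report as the primary definition and gives the dispensing data no stated part in it.

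**Conclusion.** The concern holds as a risk of differential reporting in the primary comparison, not as a demonstrated bias. Under no true effect, the chance of a false significant benefit runs from 2.5% when over-reporting is equal, through about 5% to 10% when both arms over-report but N=1 does so more, to about 11% to 21% when 5% to 8% of non-users over-report in the N=1 arm alone. These figures assume true use of 12% in both arms, 124 vs 62 evaluable, and a pooled z-test standing in for the odds-ratio interval. The plan should address this, because the data that would test it are already being recorded. It does not invalidate the design.

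**What to change.** Before any by-arm look at outcomes, pre-specify a key sensitivity analysis of the primary outcome:

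- Statin use at 12 months counts only if self-report is confirmed by a dispensing record whose supply covers the 12-month visit. The rule is the same in both arms.
- The odds ratio and 95% confidence interval are reported beside the primary result.
- Discordant reports (use reported without supply, and supply without reported use) are tabulated by arm.
- If the confirmed estimate is materially smaller, with that margin set in advance, the conclusion is limited to reported use.

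Requiring only that the two analyses point in the same direction would protect little: with equal true use, the dispensing estimate favours N=1 by chance about half the time.

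The sponsor could instead make the dispensing-confirmed outcome primary. That is a trade-off between two imperfect measures, and it would need an amendment and a registry update.

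The cost is small. No new data are collected, no clinical management changes, and the sample size stays at 247 if the 30% and 12% rates are kept. The downside is that dispensing is not ingestion. Confirmed use can also be no higher than self-reported use, so if the confirmed outcome became primary the assumed rates should be reconsidered.
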